### The EMBRACE Intervention

The EMBRACE package of interventions was developed based on formative research surveys conducted in 2012 and 2013. These surveys consisted of situation analyses, assessments of CHOs' working conditions, and analyses of the social capital in the local population. These were elaborated and carried out through close collaboration with the researchers of GHS at the: Dodowa, Kintampo, Navrongo Health Research Centers (HRC) and The University of Tokyo.

The situational analysis survey was conducted to identify the cracks in, barriers to, and

promoters of service reception in continuous MNCH care. In this survey, 1,500 women were recruited from three HDSS sites, all of whom had become pregnant within the one year preceding the survey. They were interviewed using a semi-structured questionnaire. The survey also involved qualitative study components such as key informant interviews and focus group discussions (FGDs). The key informant interviews targeted doctors, midwives, CHOs, and district officers who worked in MNCH. The FGDs targeted mothers who had become pregnant within the last one year, their husbands, and their mothers-in-laws.

Although delivery and laboratory services are provided only at the secondary and tertiary level health facilities, basic CoC services are provided even at the primary level in Ghana. ANC services include general check-ups for mothers, urine testing, hemoglobin testing, prevention of mother-to-child transmission (PMTCT) of HIV, nutritional support, tetanus immunization, and health education for birth preparedness and maternal complications. Delivery services, meanwhile, include skilled delivery, facility referral, and emergency obstetric care. Finally, PNC services include general check-ups for mothers and infants, body weight measurements, infant vaccination, hemoglobin testing, nutritional support, health education for breastfeeding and infant care, and family planning counseling. ANC and PNC services are also provided through home visits.

However, in actual practice, not all of these services are taken up consistently by mothers and infants. CoC as a concept is quite new in Ghana, and the linkages between MNCH services are weak. Consequently, most Ghanaian mothers are not conscious of the availability and importance of continuous MNCH services. In particular, rates of uptake for PNC within 48 hours postpartum have been especially low, likely due to the difficulty faced by mothers in accessing a health facility after home delivery. Moreover, assuming

the mother has no particular health issue, mother and infant are usually discharged within less than 24 hours postpartum.

In light of this context, the following four interventions were developed: utilization of an MNCH CoC card (A-1), CoC reorientation (A-2), 24-hour retention of mother and neonate post-delivery at the health facility (B-1), and PNC provided by home visit within 48 hours after delivery (B-2). Interventions A-1 and A-2 will be uniformly implemented in the intervention arm, while B-1 and B-2 will be discretionary according to the sites' resource. In the health facilities of the control arm, conventional MNCH services will be provided. Details of each intervention are explained in the following sections.

***(A-1) Utilization of maternal, neonatal and child health continuum of care card***

An MNCH CoC card for mothers will be developed to meet four objectives: 1) to encourage mothers to comply consistently with the full maternal and infant care regimen, 2) to educate mothers on the timing and schedule of the necessary MNCH services and visits, 3) to evaluate and monitor mothers' status in terms of care uptake and health-related danger signs, and 4) to establish a strong rapport between mothers and health workers. The card has been created by the Ghana EMBRACE implementation research project team based on the GHS and WHO guidelines. It was reviewed by senior GHS advisors in charge of health education, and approved by the EMBRACE Advisory Board members in February 2014.

The implementation period of this intervention is from September 2014 to **December 2015**. The card will be provided through health service providers to all women who receive ANC, delivery attendance, and PNC services via SBAs such as obstetricians, midwives, or CHOs under the supervision of a midwife. Each woman

**Table 1: MNCH CoC card contents**

| Contents         | Main components                                                                                                      |
|-------------------------|-----------------------------------------------------------------------------------------------------------------------------|
| CoC services     | -ANC (4x)
-Birth by skilled attendant
-PNC (3x)                                                                       |
| Essential services      | -Hemoglobin test
-Malaria drug (IPT)
-Tetanus toxoid injections                                                       |
| Health education | -Items for delivery and baby
-Caretaker
-Transport
-Breastfeeding counseling
-Family planning counseling |
| Danger signs            | -Identification of danger signs and associated dates                                                                        |

will receive a card at the timing of her first visit for registration with health facilities or any of the above services. Health service providers include midwives, CHOs, Community Health Nurses (CHNs), and doctors in public, private and faith-based health facilities. These cadres will provide routine MNCH care at the health facility level, at the community level, or at home. Each time a pregnant woman receives CoC services at a health facility, by outreach, or by home visit, the health service providers will put a sticker on the card to show that the mother has received CoC services. The timings at which women receive these stickers include each of the four ANC sessions, with SBA-assisted delivery, and the three PNC sessions (within 48 hours, on the seventh day, and at the end of six weeks postpartum).

Through the intervention, the women will also be educated by health workers on birth preparedness practices during ANC visits and about exclusive breastfeeding and family planning during PNC. Upon confirming that the women received these health education messages, the health workers will affix the appropriate seals on their cards. The cards will also contain other relevant information such as blood test results for hemoglobin

assessment, intermittent preventive treatment (IPT) for malaria, tetanus toxoid immunization, and danger sign records. This information is intended to help health workers to see at a glance the women's stages of care and danger signs history, with more detailed information accessible for review in the maternal health record book. The card will be stored in the mothers' handbook and kept with them.

***(A-2) Continuum of care in maternal, neonatal and child health reorientation***

The CoC in MNCH reorientation will be carried out with health administrators (supervisors of the District Health Management Team (DHMT) and Sub-district Health Team (SDHMT) and health service providers. Its purpose is to reorient supervisors and health service providers toward a solid understanding of the CoC concept in MNCH, with which they can then educate the targeted women on the importance of the CoC. The reorientation will be conducted in August 2014.

The reorientation will be implemented in two stages: training of trainers (ToT), followed by reorientation of the health service providers. The reorientation is mainly focused on introducing CoC concepts in MNCH, the importance thereof, and uses of the CoC promoting card. However, instruction will also be provided on how to conduct interventions and to supervise the DHMT and SDHMT. Each phase of instruction will take three consecutive days and be held in the local DHMT office. Training materials such as manuals and guides were developed by the Ghana EMBRACE implementation research project team during the workshop held in February 2014. All materials were created based on the various guidelines validated by GHS, WHO, and UNICEF, and approved by the EMBRACE Advisory Board members.

In the ToT phase, a master training team will be formed by the Ghana EMBRACE

researchers and regional health administration (RHA) members. This team will deliver the ToT about reorientation to DHMT/SHMT members. In each session, all DHMT/SHMT staff members with responsibility for health facility supervision will attend. The EMBRACE research members from HRCs will also attend as observers.

In the second phase of the training, RHA/DHMT/SHMT staff members who received ToT will, in turn, provide the reorientation to health service providers. Participants in this health service provider reorientation will include MNCH service providers (midwives, CHOs, CHNs, doctors, and health assistants) who work in public, private and faith-based health facilities within the study's intervention arm. Health service provider reorientation sessions will be led by RHA/DHMT/SHMT trainers and HRC researchers who attended the relevant ToT sessions.

The trained DHMT/SDHT staff members will supervise the trained health service providers through a regular monthly supervision in their catchment areas. The aim is to visit each health facility at least once a month to directly observe health providers' service provision. A standard sheet will be developed to support supervision, with space in which to record activities and issues raised.

***(B-1) 24-hour retention of mothers and their infants after delivery***

Upon delivering, women will be encouraged to stay at the health facilities for at least 24 hours with their neonates to receive PNC. The aim of this intervention is to improve the within-48-hours-postpartum PNC uptake rate of mothers and neonates. The implementation period will run from **October 2014 to December 2015**. This intervention will be conducted only in those health facilities providing delivery service by SBAs and having space for abed for postpartum rest. Approximately 5,850 women are estimated to

use this service during the intervention period. For those who are not fully followed from the first ANC to the PNC at six weeks postpartum, the impact of CoC completion will be analyzed according to the care stages they received during the intervention period. Such data may be analyzed separately from fully followed-up mothers. Intervention impacts in terms of postpartum complications will also be analyzed.

In this intervention, mothers and babies will receive necessary care in the health facility for 24 hours after delivery. During their stay, mothers will be provided nutritious food drink (Milo) offered by the Ghana EMBRACE implementation research project. After ensuring all of the necessary health check points, health service providers will discharge the mothers. In cases where mothers and/or neonates have particular symptomatic complications, midwives will provide supplementary extended care or refer to the district hospital, as appropriate. The women will be advised to come to the health facilities with their neonates for PNC on the seventh day and at the end of six weeks following delivery. If the women do not return to the health facility for PNC as instructed, the health workers will visit their homes to provide PNC service, as part of their routine follow-up duties.

#### ***(B-2) Postnatal care by home visits***

Functional CHOs will be encouraged to visit mothers and babies for PNC within 48 hours postpartum. Similar to the B-1 intervention, the aim of this intervention is to improve the within-48-hours-postpartum PNC rate for mothers and neonates. The implementation period will run from **October 2014 to December 2015**. The intervention is composed of two steps. The first step is delivery notification: in case of home delivery, Community Health Volunteers (CHVs), Community Key Informants (CKIs) or Traditional Birth Attendants (TBAs) will inform the CHOs about the labor or delivery. In the case of facility

delivery, when a woman has left the facility before the first PNC, SBAs will convey that information to CHOs so that they can visit the woman at home for PNC. The second step is PNC by home visits: CHOs will visit mothers and their neonates for PNC within 48 hours of delivery for women who delivered at home. If a woman delivers at a health facility but does not receive PNC within 48 hours, CHOs will visit her according to the information obtained from the health facilities. Approximately 8,750 women are estimated to be using this service.

The PNC by home visits will be conducted by functional CHPS zones with compounds. Targeted CHPS coverage is 50% of the total area. The estimated number of CHPS zones is 17 in Dodowa, 18 in Kintampo, and 21 in Navrongo. Delivery information will be communicated to the functional CHPS compounds via CHVs, CKIs, and TBAs. These messengers will receive two Ghana cedis (approximately 1 USD) per labor or delivery message conveyed as part of their communication fee. The money will be paid from the Ghana EMBRACE Implementation Research project budget. The women will be advised to visit health facilities for PNC on the seventh day after delivery. If the women do not come to the health facility, the CHOs will visit their homes to provide PNC service, as part of their routine follow-up duties.

## **Equipment and Materials**

Eligible health facilities will be provided abed for postpartum rest or a motorbike if necessary, as well as a set of materials that aim to assure the minimum stable implementation of the intervention. Before initiating the interventions, the study team will conduct a facility assessment for all health facilities in the study sites and investigate

available equipment and materials. If functional equipment and materials are not available, functional ones will be duly provided. Where necessary, abed for postpartum rest, rechargeable lamp/solar lantern, and torchlight will be provided for all eligible health facilities as part of the B-1 intervention. A motorbike will be provided for health facilities as part of the B-2 intervention. A set of care materials will also be provided for both eligible categories of health facility: blood pressure apparatus for mother and infant, stethoscopes, thermometers, and pen lights.

### **Quality Assurance**

In each HRC, a monitoring team will be formed. This team will be responsible for monitoring all implementation activities of health service providers and for supervision of DHMT/SDHT supervisors. They may join the DHMT/SDHT supervision and directly observe health providers' service provision and supervisors' supportive activities as well. During the initial period of the intervention (for the first four months), monthly monitoring will be undertaken, after which the frequency will decrease gradually.

### **Preparatory Activities**

Several preparatory activities will be organized to help the implementation proceed smoothly.

#### ***Stakeholder meeting***

The HRCs will organize stakeholder meetings before and after the intervention. The

purpose of the stakeholder meetings is to gain support and credibility for the intervention by eliciting the stakeholders' and the wider community's involvement and ownership in the initiative. In this meeting, the HRCs will invite RHA, DHMT, and SDHMT members from both intervention and control areas. As far as content, the Ghana EMBRACE researchers of the HRCs will present the outline of the Ghana EMBRACE implementation research project, explain the purpose of the proposed package of interventions, and discuss its implications for the health facilities. This includes a detailed discussion to harmonize messages between the research team and stakeholders, as well as feedback on findings from the formative research survey. A list of issues which may arise during the intervention period will be made at the stakeholder meeting and shared with other HRCs.

### ***Community leaders meeting***

The HRCs will also organize meetings for community chiefs and key members of the communities in the intervention arm before and after the intervention. The Ghana EMBRACE researchers of the HRCs and DHMT/SDHMT staff members will visit all intervention arm communities during June and July 2014 and hold meetings with the chiefs and key members of the communities. These meetings will aim to obtain the consent of principal community leaders to carry out the interventions in their communities. Each meeting will last one to two hours and take the form of a presentation and discussion. The questions raised during the meetings will be noted and brought to attention of the Ghana EMBRACE research team to feed into the implementation training. When the interventions have been completed in **January 2016**, a second round of community

leaders meetings will be held and the results of the intervention will be shared with the chiefs and key members of the communities.

### ***Community durbars***

Community-wide meetings will be held by HRCs and DHMT/SDHMT members in each community of the intervention arm before and after the intervention. The purpose of these meetings will be to introduce the Ghana EMBRACE implementation research project and the intervention contents, and to discuss the importance of community support for its success. Such meetings will be chaired by the community chiefs, inviting the community residents including CHVs, CKIs and TBAs to attend. Once the intervention is completed, in **January 2016**, the second community durbar will be held and the results of the intervention shared with the community.

### **Randomization**

In each HDSS site, sub-districts will be allocated to either the intervention or the control arm. Only Jema and Dumso sub-districts (which used to be a part of Jema) in the Kintampo site will be combined to form a cluster in order to match the Kintampo sub-district with respect to population and number of deliveries. In a total of three HDSS sites, 32 clusters will be set as the Ghana EMBRACE implementation research zone. From each HDSS site, half of the clusters will be allocated as the intervention arm and the other half as the control arm. Cluster stratification will be carried out using restricted stratified randomization to ensure balanced numbers of population, deliveries in each cluster, and

midwives available. Then, 16 pairs of clusters will be matched, with one of each pair being allocated randomly to either the intervention or the control arm. The random sequence of allocation will be computer-generated. Cluster randomization is preferred over individual-level randomization to minimize contamination and for pragmatic purposes with a view to the future scale-up of the intervention. Randomization will be done by a data analyst who is not a primary member of the study team.

### ***Intervention arm***

The intervention will be implemented in 16 clusters: four clusters in Dodowa, six clusters in Kintampo, and six clusters in Navrongo. Recipients of the intervention will comprise pairs of woman and their infants who have received maternal and infant services, in addition to the routine MNCH services currently available.

### ***Control arm***

The control arm will include 16 clusters: four clusters in Dodowa, six clusters in Kintampo, and six clusters in Navrongo. In the control arm, all women and infants will continue to benefit from the routine MNCH services currently available: ANC, PNC, access to free SBA-attended delivery, and routine interactions with CHOs concerning home-visit and MNCH care.

### **Participant withdrawal**

Participants will be withdrawn from the study if they:

- experience a serious or intolerable adverse event;

- develop or disclose, during the course of the study, symptoms or conditions listed in the exclusion criteria; or
- require early discontinuation for any other reason.

## **Impact Evaluation**

To evaluate the impact of the intervention package, the baseline and evaluation surveys will be conducted in three HDSS sites. The period of the baseline survey will be from July to August 2014. **The intervention period will run from October 2014 to December 2015. Period of the last three months (October to December 2015) will be added to mitigate the decline in the service quality due to the abrupt intervention cessation. The evaluation survey period will be from October to November 2015, and the survey's target will not include the mothers who would newly enter this period, thus the survey results would not be influenced by the addition of the period.**

Individual mother- and infant-level data will be collected regarding their CoC MNCH completion rates, complication rates, within-48-hours-postpartum PNC rates, mortality and adverse outcomes. In the baseline survey, data will be collected through household surveys of mothers who delivered within the two years preceding the survey. In the evaluation survey, mothers will be included if they have received any aspect of MNCH care, even in part, during the intervention period. However, for data from those who cannot be fully followed up during the intervention period, analyses will be performed according to the care stages they received during the intervention period. This may be analyzed separately from mothers who have passed the period from the first ANC session to the PNC at six weeks during the intervention period. Individual mother- and infant-level data will also be obtained from the HDSS data set regarding pregnancy outcomes

and morbidity.

To evaluate the impact of the implementation, a set of data and supporting information will be collected during the supervision by the DHMT/SDHMT. **This includes the status of CoC card distribution and actual users, as well as uptake of PNC within 48 hours postpartum, either by retention of mothers at the facilities or by home visits. In addition, qualitative data of women and health workers will be collected during the monitoring by the researchers. Those include transcript data of interview, audio-visual data (photographic and motion data) which will be collected through the in-depth interviews. Target of in-depth interview will be women and health workers who will be involved in the intervention or control arm.**

Facility-level data including availability of infrastructure, equipment, and MNCH service providers will be collected from each health facility. These data items will be used as covariates that might influence an outcome in the impact evaluation.

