### **Study Population**

Pregnant women will be recruited as participants of the study from the areas of Dodowa, Kintampo and Navrongo HDSS. Eligibility criteria will be as follows.

(i) Participants of the baseline survey:

Study population would be females who got pregnant in the target HDSS sites. The inclusion criteria are those who gave birth within the two years preceding the baseline survey, including live-births and still-births. The exclusion criteria will be those who have infants younger than six weeks of age at the beginning of the data collection.

(ii) Participants of the intervention and evaluation survey:

The study population would be females who got pregnant in the target HDSS sites. The inclusion criteria will be those who are between 16 weeks gestation and six weeks postpartum during the intervention period of A-1, B-1 and B-2 **(1st October 2014 to 31st December 2015)** including live-births and still-births. The exclusion criteria will be those who have infants younger than six weeks of age at the beginning of the data collection. From preliminary information gathered from the participating three HDSS sites, during the intervention period, about **27,500** mothers are expected to experience pregnancy, delivery, or the postnatal period in the study sites, and these will form the target population in this study. **An**

estimated total of 10,000 mothers are expected to be fully followed up from their first ANC visit to their PNC visit at six weeks post-partum (approximately 5,000 intervention and 5,000 control arms), which accounts for 36 % of all target mothers. The remaining 64% will be also followed up as they will partially receive the intervention; those who registered at their first ANC before the start of intervention, and those whose third PNC period occurs after the intervention period. See table below.

| Year                 | 2014          |   |   |   |   |   |   |                |    |    |   |   | 2015 |   |   |               |   |   |   |    |    |    |  |  |
|----------------------|---------------|---|---|---|---|---|---|----------------|----|----|---|---|------|---|---|---------------|---|---|---|----|----|----|--|--|
| Month                | 3             | 4 | 5 | 6 | 7 | 8 | 9 | 10             | 11 | 12 | 1 | 2 | 3    | 4 | 5 | 6             | 7 | 8 | 9 | 10 | 11 | 12 |  |  |

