### **Statistical Analysis**

Baseline and evaluation survey data will be analyzed to assess changes in each outcome in both intervention and control arms. To minimize overestimation of the intervention effect, all intervention impact outcomes will be estimated by intention-to-treat analysis, by which individuals are analyzed according to an allocated arm as the outcome data are

available, regardless of the place where they received the care. Also, all eligible individuals are included in the analysis, whether or not they provided outcome data.

Data collected at the individual level will be analyzed using generalized estimating equations (GEE) and mixed effects models for both continuous and binary outcomes.

Adjustment factors include items such as basic demographic characteristics and socio-economic characteristics, as well as the characteristics of facilities located in the area where the mother and infant live. Data analysis will be done primarily using Stata version 12.1. (StataCorp LP, College Station, Texas, USA).

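### The protocol sets evaluation-survey inclusion once by care received and once by pregnancy dates; taken literally, the care-based rule drops women without care from the denominators of the care outcomes

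*Protocol*

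**What the plan says.** Three parts of the protocol bear on who enters the evaluation comparison.

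- **Impact Evaluation** gives the survey's inclusion rule: "In the evaluation survey, mothers will be included if they have received any aspect of MNCH care, even in part, during the intervention period". Just before this, it sets the baseline survey to cover mothers who delivered in the preceding two years, with no condition on care.
- **Study Population**, item (ii), covers the intervention and the evaluation survey together. "The study population would be females who got pregnant in the target HDSS sites", and the inclusion criterion is "those who are between 16 weeks gestation and six weeks postpartum during the intervention period of A-1, B-1 and B-2". No care is required. The target of 27,500 is counted the same way: these "mothers are expected to experience pregnancy, delivery, or the postnatal period in the study sites".
- **Statistical Analysis** specifies intention-to-treat by allocated arm and says that "all eligible individuals are included in the analysis, whether or not they provided outcome data".

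For mothers who cannot be followed throughout, the B-1 section says that the impact on completion "will be analyzed according to the care stages they received during the intervention period", and Impact Evaluation repeats this rule. The fully followed group of about 10,000 is described as running from a first antenatal visit to the six-week postnatal visit, "which accounts for 36 % of all target mothers".

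**The concern.** The primary outcome (completion of the continuum of care) and the second outcome (postnatal care within 48 hours) both measure receipt of care. A woman with no care fails both. If inclusion requires some care during the intervention period, these certain failures leave the denominator and each arm's rate rises. Contact is also something the package tries to change: under B-2, volunteers and birth attendants notify health officers of home deliveries so that the mother is visited. The share of women left out could therefore differ by arm, which would be selection after randomisation.

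Two further problems follow from the same wording. The baseline survey has no care condition, so the planned before-and-after changes would compare unlike denominators. And if partly followed mothers are analysed by the stages they received, a stage enters the denominator only when it was received, so its uptake says nothing about the arms.

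**Working it through.** **The protocol's own figures.** The groups in Figure 2 add up: 8,750 + 10,000 + 8,750 = 27,500. Full follow-up is 10,000 / 27,500 = 36.4%, stated as 36%. Partial follow-up is 17,500 / 27,500 = 63.6%, stated as 64%. All of these reproduce, and all are counted by dates, not by care received.

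**Inputs.** Completion of 10% before the trial is given in Rationale for Study. The protocol does not give the share of women with any care, so control shares of 80% to 98% and intervention shares of 95% to 99% are assumed. The true contrasts of 10% v 20% (completion) and 40% v 60% (postnatal care within 48 hours) are also assumed.

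**Formula.** Let p be the true rate in an arm and a the share with any care. Women with no care contribute no successes, so

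observed rate = p / a

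observed RR = true RR × a(control) / a(intervention)

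This is exact for women whose relevant stages all fall within the intervention period.

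| Any care, control / intervention | Factor on RR | Completion, true 10% v 20% (RR 2.00) | Postnatal care within 48 h, true 40% v 60% (RR 1.50) |
|---|---|---|---|
| 98 / 99% | 0.98/0.99 = 0.99 | 10.2% v 20.2%: 10.0 points, RR 1.98 | 19.8 points, RR 1.48 |
| 95 / 98% | 0.95/0.98 = 0.97 | 10.5% v 20.4%: 9.9 points, RR 1.94 | 19.1 points, RR 1.45 |
| 90 / 98% | 0.90/0.98 = 0.92 | 11.1% v 20.4%: 9.3 points, RR 1.84 | 16.8 points, RR 1.38 |
| 80 / 95% | 0.80/0.95 = 0.84 | 12.5% v 21.1%: 8.6 points, RR 1.68 | 13.2 points, RR 1.26 |

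With no true effect on completion (10% in both arms), the observed RR equals the factor: 0.99, 0.97, 0.92 and 0.84.

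**Equal shares.** The RR is unchanged, but the difference is divided by the common share. At 90% in both arms, 20/0.90 − 10/0.90 = 22.2 − 11.1 = 11.1 points instead of 10.0.

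**Change from baseline.** Suppose completion stays at 10% and 90% of women have any care. The baseline survey would show 10% and the evaluation survey 10/0.90 = 11.1%, an apparent rise of 1.1 points with nothing changed.

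**Date-based denominator.** Under the Study Population rule, a does not enter and this distortion is zero.

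**Stages received.** If a stage counts only when received, uptake = received / received = 100% in both arms, whatever the package does.

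**The case against.** The sentence says that mothers are included if they had care; it does not say only if. Its qualifier about partial receipt, and the sentences after it, suggest that its purpose is to admit partly exposed mothers. The formal eligibility section has no care condition, and the analysis section covers all eligible individuals. Partly followed mothers are contrasted with those who passed through the whole period, and Figure 2 groups them by month of conception, so stages received may be loose wording for stages falling in the period. Women with no contact may also be few. Navrongo reports almost 90% facility delivery and early postnatal care, and about two-thirds of Kintampo women deliver in facilities. B-2 is discretionary, with 50% target coverage, and control women keep routine health-officer contact. If the package raises contact, the distortion runs towards the null.

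Much of this stands. The benign reading may be the intended one, and size and direction are not known. But the intention-to-treat statement cannot settle the matter, because who counts as eligible is what the two sections disagree on. Field staff who follow the Impact Evaluation sentence would pass over a woman with no care, and no later analysis can recover survey data from women never interviewed.

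A reader might infer three stronger points that the documents do not support:

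- *The arm comparison is already selected.* This needs both the exclusive reading and a difference between arms in the share without care. Neither is established.
- *Perinatal mortality is biased by losing the highest-risk women.* Impact Evaluation also takes pregnancy outcomes from the surveillance data, and Study Setting says that these cover residents of all households.
- *The number of women with only the six-week visit left at the start can be read off Figure 2.* That figure is by month of conception from March 2014. Women who delivered shortly before October 2014 conceived earlier and lie outside it.

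**Conclusion.** The point holds as an unreconciled contradiction over who enters the evaluation survey, together with a loosely worded denominator for about 64% of target mothers. It concerns the denominator of the primary outcome. Any bias is conditional on the care-based rule being applied literally and on shares that the protocol does not report. For completion, the effect on the risk ratio runs from negligible (factor 0.99) to material (0.84, at the extreme assumed shares of 80% v 95%). It would inflate the ratio only if contact were lower in the intervention arm. What makes it worth settling before fieldwork is that the loss cannot be repaired afterwards.

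**What to change.** - In Impact Evaluation, replace the care-based sentence with the Study Population rule: include every resident woman on the surveillance register whose dates meet the window, whether or not she received any care.
- In the B-1 section and in Impact Evaluation, analyse partly followed mothers by the stages that fell due by date during the intervention period.
- Count a stage that was due but missed as not received, and count women with no care as not having received the stages due to them.
- Define the full-follow-up group by gestation and delivery dates, not by attendance at a first antenatal visit.

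The cost is low: two rules reworded and one subgroup definition. The surveillance system already records pregnancies and births in all households, so the sampling frame exists. Reported uptake rates will be slightly lower, because women without care now count.
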